### Procedure

We employ three recruitment strategies. First, we distribute flyers on the university campus. Second, we post advertisements on Dutch websites for mental health issues. Third, advertisements are posted on Facebook and Twitter. The flyers and advertisements specifically target people who experience low mood or mood fluctuations and direct them to a website (www.moodmonitor.nu) that contains more detailed information. Interested individuals can apply to participate in the study via this website by completing the screening questionnaire (PHQ-9, age, possession of an Android-compatible smartphone), after which they can read the study information again and can agree to participate by entering a valid email address (electronic informed consent). Applicants who do not meet the inclusion criteria will be notified instantly. If they are excluded because they score above 15 on the PHQ-9, they are advised to contact their general practitioner. Participants who meet the inclusion criteria will be randomised equally to the three groups, i.e. 1:1:1. An independent researcher performs the allocation using a computerised random number generator. Next, participants are sent a link to the baseline questionnaire (CES-D, demographics), and participants in groups 1 and 2 receive an email with instructions to download and install the MoodMonitor app on their smartphones. Even though we do not notify participants directly as to which group they are randomised, they can find out easily by reading through the study information on the website, and therefore participants cannot be considered to be blinded. After week 6 and after week 12 participants in all three groups are sent an email containing a link to the questionnaires (CES-D at week 6, CES-D and SUS at week 12). Participants who complete a measurement are offered 7.50 Euro, i.e. 22.50 for all three measurements, and an additional 10 Euro if they respond to 80 % or more of the EMA prompts. Participants will receive this incentive in the form of an electronic gift voucher sent to their email address. We will continue recruitment until 160 applicants have been randomised. Data collection runs from April 2016 to November 2016. This trial’s results will be published on the study homepage when the scientific papers concerning the main objectives have been published.

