### Analyses

The primary outcome is the effect of EMA on depressive symptoms as measured by the CES-D at T6 and T12, comparing both EMA groups with the control group. To test this on all available data, we will conduct a mixed models repeated measures regression analysis, with T6 and T12 CES-D data as the dependent variable, and baseline CES-D scores, group (1, 2, 3), time (T6, T12) and the time*group interaction as independent variables. Effects will be expressed in terms of percentage of variance explained and Cohen’s d (by dividing raw regression parameter point estimates and confidence intervals by the pooled CES-D standard deviation).

For our secondary analysis, we will examine the EMA response rate over time, which gives an indication of response fatigue. Response fatigue will also be analysed by assessing response accuracy, here defined as a declining correlation over time between theoretically associated measures. Literature has shown that mood swings are associated with higher depressive symptoms [23]. Therefore, we will analyse the variance of the EMA and its correlation with the CES-D scores, taking into account the EMA ratings of the two weeks prior to the CES-D (i.e. weeks 5 and 6 for T6 and weeks 11 and 12 for T12). A decreasing variance of EMA ratings (i.e. increasingly stable responses) will result in a decreasing correlation coefficient (*r*) with the CES-D scores if the CES-D scores do not decrease. This might indicate a decline in validity.

We will maintain a family-wise two-tailed *p*-value of .05 using the Holm-Bonferroni method [24]. IBM SPSS Statistics 23 [25] and R [26] will be used for all analyses.

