### Sample size

For the sample size calculation, we assume that a difference between either EMA group and the control group within the margin −0.25< Cohen’s d <0.25 is clinically negligible. Therefore, a difference between groups of d = 0.25 should reach statistical significance in our analysis. We ran a power calculation in G*Power [27] for a repeated-measures analysis of variance (ANOVA), which is essentially the same analysis as linear mixed modelling when there are no missing values. A total number of 120 participants (40 per group) is required in order to obtain d = 0.25 with three assessment waves, a targeted power of .85, a significance level alpha of .05, and conservative estimations of correlations between measurements (*r* = .65) and variances of the differences between groups (non-sphericity correction epsilon = .8). Expecting 25 % drop-out at T12, we will recruit 160 participants. All participants will be included in the linear mixed model, which is robust for missing data.

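### The plan says all participants enter the mixed model, but the stated model needs a baseline CES-D, collected after unblinded allocation, and at least one follow-up CES-D

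*Protocol article*

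**What the plan says.** All references are to the protocol article.

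- **Sample size**, directly after the 25% drop-out allowance: "All participants will be included in the linear mixed model, which is robust for missing data".
- **Analyses**, data used and type of model: "To test this on all available data, we will conduct a mixed models repeated measures regression analysis".
- **Analyses**, outcome, which leaves out the baseline wave: "with T6 and T12 CES-D data as the dependent variable".
- **Analyses**, predictors: "baseline CES-D scores, group (1, 2, 3), time (T6, T12) and the time*group interaction as independent variables". No imputation is described.
- **Procedure**, order of events: "Participants who meet the inclusion criteria will be randomised equally to the three groups, i.e. 1:1:1", and only then "Next, participants are sent a link to the baseline questionnaire (CES-D, demographics". The EMA groups are emailed their app instructions at this same step. The section also says that participants can work out their group and cannot be regarded as blinded.
- **Procedure**, stopping rule for recruitment: "We will continue recruitment until 160 applicants have been randomised". The count is of people randomised, not of people with a baseline score.
- **Procedure**, screening: the PHQ-9 is completed before consent and allocation, and eligibility depends on it, so every randomised participant has one.

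**The concern.** A likelihood-based mixed model keeps a participant who has one of two outcomes. It does not keep a participant who has no outcome, and software drops every row in which a covariate is missing. The inclusion sentence therefore describes a property that the specified model lacks.

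The two routes out of the model differ in importance. A participant with neither T6 nor T12 has nothing to say about the group contrast at follow-up, so little is lost. A participant with T6 or T12 but no T0 does have such information, and the model discards it. Whether T0 is returned is decided after allocation, by people who can tell which group they are in, at the moment when two of the three groups are also asked to install an app. Selecting the analysis set on that response can unbalance groups that randomisation had balanced, and a pre-randomisation severity score for everyone goes unused. Readers would also believe that all 160 were analysed when they may not have been.

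**Working it through.** **1. The plan's own figure.** Inputs from Sample size: d = 0.25 (f = d/2 = 0.125), 3 groups, 3 waves, correlation .65, epsilon .8, alpha .05, N = 120. For the within-between interaction of a repeated-measures ANOVA:

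- noncentrality = f² × N × waves × epsilon / (1 − r) = 0.015625 × 120 × 3 × 0.8 / 0.35 = 12.86
- df1 = (3 − 1)(3 − 1) × 0.8 = 3.2; df2 = (120 − 3)(3 − 1) × 0.8 = 187.2
- power = 0.851

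The smallest balanced N for .85 is 120, and 120 / (1 − 0.25) = 160. Both stated numbers reproduce.

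**2. Who has a usable row in the Analyses model.**

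| T0 | T6 or T12 | In the model? |
|---|---|---|
| present | at least one | yes |
| present | neither | no (no outcome) |
| missing | at least one | no (covariate missing, observed outcome discarded) |
| missing | neither | no |

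**3. How many enter.** From the article: 160 randomised and 25% without T12, so 160 × 0.25 = 40. Not in the article, so varied here: the share *s* of those 40 who also lack T6, and the share *b* with no T0, taken as independent of follow-up loss. Expected number in the model = (160 − 40*s*) × (1 − *b*).

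| *b* (assumed) | *s* = 0 | *s* = 0.5 | *s* = 1 |
|---|---|---|---|
| 0 | 160 | 140 | 120 |
| 5% | 152 | 133 | 114 |
| 10% | 144 | 126 | 108 |
| 20% | 128 | 112 | 96 |

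Fitting the stated model to simulated data for 160 participants gave exactly the first row, and counts within 2 of the other rows. The inclusion sentence is true in one cell only: no T0 missing and nobody missing both follow-ups.

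**4. What each route costs.**

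- *No follow-up.* A simulation used 160 participants, correlation .65, a true T12 effect of −0.25, complete T0, covariances treated as known, and total follow-up loss that was higher in the EMA groups and depended on T0 (2000 runs). The stated model gave a mean of −0.248 (SD 0.161). A three-wave model with a common T0 mean, which keeps the T0-only participants, gave −0.249 (SD 0.160). Keeping them makes no practical difference.
- *No T0.* If missing T0 is unrelated to group and prognosis, dropping a share *b* multiplies standard errors by about 1/√(1 − *b*): 1.03, 1.05 and 1.12 for 5%, 10% and 20%. That is modest. The larger risk is selection after allocation, and the article gives nothing from which to size it.

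**The case against.** The fair reading on the other side is that the sentence follows the 25% drop-out figure and means only that drop-outs are not removed as they would be in a completers-only ANOVA. The Analyses section does say that all available data are used. For the one loss that the article quantifies, missing T12, this is right: anyone with T0 and T6 stays in. The article also does not rule out imputing a missing baseline, and details of missing-data handling are often left to an analysis plan. This makes the sentence understandable but not correct. It says all participants, and the article specifies a model for which that fails.

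Several stronger readings are tempting, and the documents do not support them:

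- *The sample size is wrong.* It is not affected by this point. With complete baselines, even the worst follow-up pattern leaves 120, the number required.
- *An intention-to-treat claim is breached.* The article does not use that term or define such a set.
- *A particular number will be lost, such as 20 of 160.* That needs an assumed half of the drop-outs to miss T6. The article gives T12 drop-out only, and zero loss by that route is possible.
- *Differential loss will bias the comparison.* The design makes this possible, but no loss rate by group is given.
- *The lack of a stated missing-data assumption or a sensitivity analysis is itself a fault.* A condensed article commonly leaves both to the analysis plan.

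**Conclusion.** The inclusion sentence is false as written for the model that the article specifies. That model analyses participants with a T0 CES-D and at least one of T6 and T12. The size is uncertain: 120 to 160 of 160 with complete baselines and 25% drop-out at T12, and fewer with any missing T0, at rates that have to be assumed. The part worth acting on is the loss of participants who have follow-up scores but no T0, because it discards observed outcomes on a criterion met after unblinded allocation and is cheap to avoid. Participants with no follow-up add essentially nothing to the contrast under either model, so their absence needs only accurate wording. The conclusion assumes that no imputation of T0 is planned elsewhere. If one is, only the sentence needs correcting.

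**What to change.** Keep every participant who has at least one follow-up CES-D, by one of two routes.

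1. **Without changing procedures.** Keep T6 and T12 as outcomes, add the screening PHQ-9 as a covariate, and impute a missing T0 CES-D using the PHQ-9, by a rule fixed before the data are released. The T0 CES-D stays in the model for those who have it, so the same-scale baseline is not given up. Swapping it for the PHQ-9 would give it up, and would still leave T0-only participants without an outcome row.
2. **With a change of procedure.** Collect T0 before allocation, then fit T0, T6 and T12 as outcomes with one T0 mean common to all groups. The common mean is justified only if T0 precedes allocation, so this route does not suit the procedure as written.

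Under either route, restate the Sample size sentence along these lines: *all participants with at least one follow-up CES-D will be included, assuming data are missing at random.*

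The cost of the first route is a little more analysis work with the same data and software. The second also changes the enrolment sequence. Both give a less favourable inclusion statement than the present one. The target of 160 stays.

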## Discussion

This study aims to investigate whether self-rated EMA of depressive symptoms could induce assessment reactivity among mildly depressed individuals. The linear mixed model analyses can show an effect of Cohen’s d >0.25 (and < −0.25) on retrospectively measured depressive symptoms between groups. The 12-week study period and repeated measures design enable us to detect both short-term (6 weeks) and longer-term (12 weeks) effects on retrospectively measured depressive symptoms, as well as response fatigue.

### Implications

This study will give a first indication of EMA reactivity on depressive symptoms. An effect of EMA on depressive symptoms would limit EMA as an instrument, because a change in EMA ratings might be attributed to the EMA itself instead of treatment or other factors. This is of immediate interest to research projects in which participants carry out EMA over longer periods, such as the E-COMPARED project [8]. However, a positive effect would indicate that EMA can be applied as an intervention, e.g. alongside psychotherapy or pharmacotherapy. A negative effect would indicate that it may not be ethical to use EMA as an instrument. If we find indications of response fatigue at T6 and/or T12, we can recommend the optimal period of conducting EMA.

### Limitations

First, a change in retrospectively measured depressive symptoms could be attributed not only to a change in depression severity, but also to a change in response behaviour. If we find an effect, we can explore changes in response behaviour by testing the CES-D outcomes for measurement invariance [28]. Second, one of our secondary aims is to investigate response rate, but the response rate might be artificially high, because participants are given a monetary reward when they complete 80 % or more of the EMA prompts. This reward is necessary to answer the primary research question, because any effect of EMA can only be shown when participants conduct EMA.

### Conclusion

To our knowledge, this is the first study to investigate whether self-rated EMA of depressive symptoms could induce assessment reactivity among mildly depressed individuals.

## Abbreviations

CES-D: Centre for epidemiologic studies depression scale
EMA: Ecological momentary assessment
PHQ-9: Patient health questionnaire
SUS: System usability scale
